**Figure 3 F3:**
[figure not shown]
**Study protocol of 'STem cell Application Researches and Trials In NeuroloGy-2’ (STARTING-2) study at each timepoint.** *Indicates 1 day before mesenchymal stem cell (MSC) infusion in the MSC group vs 30 days (± 2 days) after randomization in the control group. †MSC group only. ‡Will be performed at 14 days after MSC transplantation.

Multimodal brain MRI including structural MRI, resting-state functional MRI (RS-fMRI) and diffusion tensor imaging (DTI) and motor evoked potentials (MEPs) will be performed. Multimodal MRI and MEPs techniques are described in the Additional file 1. Exploration of biomarkers is planned to further investigate the mechanisms of action of MSCs and to find predictors for response to cell therapy. Biomarkers will include SDF-1α (a chemokine), S100β (a marker of protection and regeneration), hypoxia-inducible factor 1α (HIF-1α, a marker of preconditioning), circulating MSCs and MSC-derived microvesicles, brain-derived neurotrophic factor (BDNF) and vascular endothelial growth factor (VEGF) levels, and BDNF genetic polymorphisms (Table 3) [7,18,61-64].

**Table 3 T3:** Study endpoints

**Objective**	**Endpoint**
Primary endpoint of efficacy:	
Functional outcome	Categorical shift in mRS at 90 days after treatment
Secondary endpoints of efficacy:	
Disability	Change in NIHSS between pretreatment and 90 days post-treatment ≥5 points improvement or score of 0 to 2 on NIHSS score at 14 days after treatment
Functional outcome	mRS ≤2 at 90 days after treatment
	Change of mRS between pretreatment and 90 days post-treatment
	mBI ≥60 at 90 days after treatment
	Change of mBI between pretreatment and 90 days post-treatment
Further demonstration and characteristics of motor recovery	Change of gross motor function between pretreatment and 90 days post-treatment
	Motricity index and Fugl-Meyer assessment (upper, lower)
	Change of fine motor function between pretreatment and 90 days post-treatment
	Purdue pegboard test (simple) and box and block test
	Change of mobility between pretreatment and 90 days post-treatment
	Functional ambulatory category and 10-m gait speed
Cognition	Change of MMSE between pretreatment and 90 days post-treatment
Quality of life	Change of EQ-5D between pretreatment and 90 days post-treatment
Secondary endpoints of safety:	
Death	All causes of death
Recurrence	Recurrent stroke or transient ischemic attack
The immediate reaction	Allergic reactions (tachycardia, fever, skin eruption, leukocytosis)
	Local complications (hematoma or local infection at the site of bone marrow aspiration)
	Vascular obstruction (tachypnea, oliguria, or peripheral vascular insufficiency)
	Systemic complications (infections, AST/ALT, or BUN/Cr levels)
Long-term adverse effects possibly related to MSC treatment	Tumor formation (physical examination, plain X ray, f/u MRI at 90 days after treatment)
	Aberrant connections (newly diagnosed seizure or arrhythmia)
Other parameters related to efficacy:	
Exploration of biomarkers to further demonstrate the mechanism of action and genetic profile	SDF-1α (chemokine)
	S100β (protection and regeneration)
	HIF-1 (preconditioning)
	Circulating MSCs and MSC-derived microparticles
	BDNF levels and polymorphisms and VEGF levels
Multimodal MRI	Resting-state functional MRI and diffusion tensor imaging
Neurophysiologic study	Motor evoked potentials

*ALT* alanine aminotransferase, *AST* aspartate aminotransferase, *BDNF* brain-derived neurotrophic factor, *BUN* blood urea nitrogen, *Cr* creatinine, *DWI* diffusion-weighted image, *EQ-5D* EuroQol Five Dimensions, *HBV* hepatitis B virus, *hCG* human chorionic gonadotropin, *HCV* hepatitis C virus, *HIF* hypoxia-inducible factor, *mBI* modified Barthel index, *MCA* middle cerebral artery, *MMSE* Mini-Mental State Examination, *mRS* modified Rankin Score, *MSC* mesenchymal stem cell, *NIHSS* National Institutes of Health Stroke Scale, *SDF-1α*, stromal cell-derived factor 1α, *VEGF* vascular endothelial growth factor.

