#### Improving efficacy of MSC therapy and ischemic preconditioning

Efforts to improve the efficacy of MSCs include ischemic preconditioning [41,42], blood–brain barrier (BBB) manipulation [43], and use of genetically modified MSCs (although this is not feasible in clinical practice) [44,45]. Ischemic preconditioning enhances ischemic tolerance in various tissues including heart and brain [46,47]. Clinical and preclinical studies of cerebral ischemia demonstrated that brief, non-lethal ischemia and reperfusion, referred to as ischemic preconditioning, can have a protective effect against further episodes of brain ischemia [46,48]. The cytoprotective effect of preconditioning also enhances the survival of transplanted stem cells [49]. Ischemic preconditioning before transplantation of the donor cells might initiate survival signaling, creating a primed and activated state in these cells, and reinforcing their ability to withstand harsh microenvironments after transplantation [50]. Hypoxic preconditioning is used in most preclinical studies, with stem cells exposed to 0.5% to 3% oxygen for 24 to 72 h.

The number of clinical trials using allogeneic-based cell therapy approaches is growing [51]. However, treatment using bone marrow stromal cells from stroke rats was found to promote more improvement of functional outcomes in a rat stroke model compared to cells from normal rats [52]. Thus, it is conceivable that MSCs from patients with acute stroke could have different characteristics from cells from healthy individuals (either allogeneic or chronic stroke donors), and culture expansion using serum obtained during the acute phase of stroke could improve the therapeutic effects of MSCs. We recently conducted preclinical studies on the effects of ischemic preconditioning with ischemic serum on MSC functions (unpublished data). We evaluated the characteristics of rat MSCs after culturing with FBS or serum obtained from a rat stroke model. Compared to FBS, the use of serum from the rat stroke model resulted in more rapid MSC expansion, which reduced the cell preparation time by increasing the G2/M phase, decreasing cell death/senescence, increasing trophic factor secretion, and migration capacity.

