**Figure 2 F2:**
[figure not shown]
**Overall study flow of the 'STem cell Application Researches and Trials In NeuroloGy-2’ (STARTING-2) study.** *Indicates 1 day before mesenchymal stem cell (MSC) infusion in the MSC group vs 30 days (± 2 days) after randomization in the control group.

**Table 2 T2:** Inclusion and exclusion criteria

**No.**	**Criteria type**
Inclusion	
1	Men or women (women must be of non-child-bearing potential), age 30 to 75 years
2	Stroke observed within 90 days of the onset of symptoms
3	Radiological:
	Relevant lesions within the MCA territory as assessed using DWI.
	Maximum diameter of the stroke region in any dimension ≥15 mm
	Damage not involving more than a half of the ipsilateral subventricular zone^a^
4	Clinical (National Institutes of Health Stroke Scale (NIHSS)):
	a. Moderate to severe persistent neurologic deficit (NIHSS of 6 to 21 inclusive)
	b. New onset of extremity paresis on the affected side, defined as a score of 2 to 4 on the NIHSS motor arm (item 5) or leg (item 6) question.
	c. Alert or drowsy but easily arousable as defined by score of 0 to 1 on the NIHSS level of consciousness question (item 1A).
	d. 'Slow recovery’ defined as change in NIHSS ≤1 point/3 days
5	Willingness:
	a. Reasonable likelihood of receiving standard physical, occupational and speech rehabilitation therapy as indicated for post-stroke deficits
	b. Able to participate in the evaluation process to the point of accurate assessment
	c. Willing and able to comply with scheduled visits, lifestyle guidelines, treatment plan, laboratory tests, and other study procedures
	d. Evidence of a personally signed and dated informed consent document
6	Use of antiplatelet, anticoagulant and/or antithrombotic agents is acceptable
Exclusion	
1	Presence of significant disability prior to the current stroke, defined as pre-stroke modified Rankin score of 2 or more
2	Stroke that is either:
	a. Lacunar infarction
	b. Hematologic cause of stroke
	c. Recurrent or progressive stroke within 1 week at the time of screening
3	Hematologic disorders or bone marrow suppression
4	Severe medical illness defined as:
	a. Severe heart failure
	b. Severe febrile illness
	c. Hepatic or renal dysfunction
	d. Active cancer
	e. Any evidence of chronic comorbid condition or unstable acute systemic illnesses which, in the investigator’s opinion, could shorten survival or limit ability to complete the study
5	Presence of HIV, HBV, HCV, or syphilis on admission blood tests

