#### Sample size and statistical analysis

Approximately 60 participants (MSCs vs control group = 40:20) will be studied. This sample size was chosen to provide a power of 80% and an alpha level of 5% to detect a common odds ratio of 4.75 (across all cut-off points of the mRS), which was the result from the STARTING trial [7]. Possible harmful effects of MSCs will be determined and assumptions underlying the sample size calculation will be adjusted by an interim analysis performed by an independent data and safety monitoring committee (data from 20 eligible participants in the MSC group) [65].

All randomized participants will be included in the endpoint analyses on an intention-to-treat basis. For primary outcome analysis, the categorical shift of mRS at 90 days after treatment will be compared between the MSC and control groups using the Cochran-Mantel-Haenszel shift test and proportional odds logistic regression analysis adjusted for age, sex, stroke mechanisms, and infarct volume on fluid attenuation inversion recovery (FLAIR) imaging 1 day before MSC infusion in the MSC group or 30 days (± 2 days) after randomization in the control group. In this study, the adjusted result is prespecified as the primary outcome analysis. Secondary and exploratory analyses will be performed according to standard statistical methods as appropriate.

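### On the natural reading, Table 3's change endpoints subtract a baseline taken after randomisation, on a different clock in each arm

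*Protocol article*

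**What the plan says.** Table 3 (Study endpoints) sets most secondary efficacy endpoints as changes over one interval. The motor rows follow the pattern "Change of gross motor function between pretreatment and 90 days post-treatment", and the last row reads "Change of EQ-5D between pretreatment and 90 days post-treatment". Ten scales are defined this way: mRS, mBI, Motricity index, Fugl-Meyer, Purdue pegboard, box and block, functional ambulatory category, 10-m gait speed, MMSE and EQ-5D. The NIHSS row also starts from a pretreatment change but goes on to "≥5 points improvement or score of 0 to 2 on NIHSS score at 14 days after treatment", so one part of it is a score that needs no baseline.

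Table 3 does not say what pretreatment means for a control patient. The footnote to the figure of assessments by timepoint (Figure 3) marks a visit as "1 day before mesenchymal stem cell (MSC) infusion in the MSC group vs 30 days (± 2 days) after randomization in the control group", and Figure 2 carries the same footnote. The section Sample size and statistical analysis uses the same pair of days for infarct volume: "1 day before MSC infusion in the MSC group or 30 days (± 2 days) after randomization in the control group".

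Under Preparation and transplantation of MSCs, marrow is aspirated in the MSC group within 1 week of randomisation. Cells are then grown to a confluence target and expanded to a dose target. No infusion day is given.

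**The concern.** A change score compares randomised groups fairly if its starting value was fixed before allocation could affect it. Here the starting value appears to be measured weeks after allocation. In the MSC arm it follows a marrow aspiration that controls do not have, and its date depends on how fast that patient's cells grow. In the control arm its date is a calendar day. The two arms may therefore start from different points on the recovery curve, and the subtraction turns that difference into an apparent effect.

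Any loss of function between randomisation and infusion is also absorbed into the baseline. Secondary objective (a) rests on serial motor assessment and functional outcome. The article's own section on outcome measurement argues that the traditional scales may be too insensitive for cell therapy, so readers will look to these motor endpoints.

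**Working it through.** The documents give no figure for the change endpoints, so there is none to reproduce. The planned total of 60 concerns the primary mRS shift and does not bear on this point.

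**Inputs from the article.** Control visit at day 30 ± 2 after randomisation; MSC visit 1 day before infusion; final assessment 90 days after treatment; entry up to 90 days after onset; recovery at entry of at most 1 NIHSS point per 3 days (inclusion criterion 4d); NIHSS improvement cut of 5 points.

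**Assumed inputs.** Recovery R(t) = 40 × (1 − exp(−t/τ)) points at t days after stroke, with τ = 35 (range 25 to 50); randomisation at day 14; no treatment effect; MSC pretreatment visit 7 days earlier than the control visit; both arms followed for 90 days from that visit.

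1. Control: baseline at 14 + 30 = 44 days, end at 134. Change = 40 × (exp(−44/35) − exp(−134/35)) = 40 × (0.284 − 0.022) = 10.5.
2. MSC: baseline at 37 days, end at 127. Change = 40 × (exp(−37/35) − exp(−127/35)) = 40 × (0.347 − 0.027) = 12.8.
3. Spurious difference: 12.8 − 10.5 = +2.3 points.
4. The final level differs by only 40 × (0.022 − 0.027) = −0.2. Nearly all of the artefact therefore comes from the subtracted baseline, where the MSC arm sits 40 × (0.347 − 0.284) = 2.5 points lower.
5. Over τ = 25 to 50 the 7-day result is +2.1 to +2.3 points.
6. Reverse direction: with the MSC visit 7 days later, the difference is 10.5 × (exp(−7/35) − 1) = −1.9 points.
7. Late entry: moving randomisation from day 14 to day 60 multiplies the bias by exp(−46/τ), giving about 0.3 to 0.8 points for the 7-day offset. At day 90 it is about 0.1 to 0.5.

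A second grid (τ = 21 to 60, randomisation at day 7, MSC baseline 1 day before infusion) expresses the bias as a percentage of total recoverable function:

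| Infusion day after randomisation | Spurious MSC minus control change |
|---|---|
| 20 | +8.7 to +12.0 |
| 30 | about +1 |
| 40 | −5.7 to −7.2 |
| 50 | −10.1 to −13.4 |

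With randomisation at day 90 it never exceeds 2.8 in size.

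**NIHSS, from the article's own ceiling.** At 1 point per 3 days, a 10-day misalignment is worth at most 10/3 = 3.3 points against the cut of 5. The ceiling applies at screening, and the rate a month later should be lower.

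**Loss before infusion.** Suppose the MSC arm loses 4 points between randomisation and infusion, and there is no other effect. Measured from the pretreatment visit, the contrast is 0 if the loss persists and +4 if it resolves. Measured from a pre-randomisation value, it is −4 and 0.

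**Check of the fix.** With a pre-randomisation baseline and the final visit on the same day after randomisation in both arms, the spurious difference is 0. If only the baseline is moved, a residual of −2.2% to +3.4% of recoverable function remains over the grid, because 90 days after treatment is also arm-specific.

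**The case against.** The strongest objection is that no visible text says Table 3's pretreatment value comes from the asterisked visit. The asterisk belongs to figures that are not shown, and Figure 3 may settle when each scale is taken. The statistical section ties that visit only to infarct volume. This stands, and the point is therefore conditional. It still has weight: no other two-arm pretreatment time is given, and Table 3 needs to say which visit it means.

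A reader might infer that the bias will favour MSC, because the article reports that serum from stroke rats "resulted in more rapid MSC expansion, which reduced the cell preparation time". That is unpublished rat-cell work compared with fetal bovine serum. It says nothing about human culture time relative to day 30, and day 30 may already reflect the expected culture time. Neither a direction nor a systematic offset is supported.

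A reader might also infer that harm before infusion would be hidden from the trial. It would not: the primary 90-day mRS, mRS ≤2 and mBI ≥60 subtract nothing and would show a persistent loss. No document suggests that the pre-infusion procedures do cause functional loss.

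Finally, the rule that "All randomized participants will be included in the endpoint analyses on an intention-to-treat basis" might seem contradicted by patients who never reach the pretreatment visit. That is ordinary missing-data handling, which can be left to the analysis plan, and is no finding here.

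It can fairly be said that the article leaves secondary analyses to standard methods, so a plain test on raw change is not fixed. But the endpoint itself is defined as the change, and adjusting for a post-randomisation value in place of subtracting it would not restore a common origin.

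**Conclusion.** The point holds conditionally. If pretreatment is the asterisked visit, the ten change scores and the change part of the NIHSS rule do not compare the randomised groups from a common origin. The bias takes its sign from whether infusion averages before or after about day 30, and is near zero if it averages about day 30 or if patients enter late after stroke. The figure of about +2.3 points for a 7-day-earlier infusion rests on an assumed curve, an assumed randomisation day and an assumed offset. Neither the infusion day nor the recovery curve is in the documents, so the actual size cannot be derived from them. Separately from any timing offset, functional loss before infusion drops out of these change scores if it persists and counts as improvement if it resolves. The change endpoints are secondary and the repair is cheap, so the change should be made, but the point does not by itself undermine the trial.

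**What to change.** In Table 3, define the baseline of each change endpoint as the last value before randomisation, and analyse the 90-day score adjusted for it. Entry NIHSS exists for every patient as an inclusion criterion. The visible text does not establish that the other scales are taken before randomisation. For any that are not, compare the 90-day score adjusted for entry NIHSS, without subtracting the pretreatment value. Keep the pretreatment value as descriptive.

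Also state the final assessment on a common clock from randomisation in both arms. Failing that, report the actual days from randomisation and adjust for the small remaining difference.

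If pretreatment already means the entry visit, a sentence in Table 3 saying so settles the baseline.

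The baseline change needs only wording in Table 3 and the analysis plan, with no new patients; putting the final assessment on a common clock may move a visit date. The downside is slightly wider confidence intervals, because an earlier baseline correlates less with the 90-day score.

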#### Preparation and transplantation of MSCs

Methods for bone marrow aspiration, MSC isolation, cell preparation, and intravenous infusion will be as previously described, except for the amount of aspirated bone marrow and the use of autologous serum for *ex vivo* cultivation of MSCs [6,7]. Briefly, 60 mL of bone marrow will be aspirated from both posterior iliac crests of each patient in the MSC group. Aspiration will be performed within 1 week after randomization to the MSC group. Bone marrow mononuclear cells will be separated by Ficoll density centrifugation.

We will use autologous MSCs prepared with autologous serum, instead of FBS. Serum for ischemic preconditioning will be obtained at the earliest time possible, immediately after randomization. Less than 500 mL of whole blood will be drawn at any one time.

Mononuclear cells will be cultured in a 175 cm^2^ flask (Falcon, Franklin Lakes, NJ, USA) in low-glucose Dulbecco’s modified Eagle medium (Gibco-BRL, Grand Island, NY, USA) supplemented with 10% autologous serum and 20 μg/mL gentamicin in a humidified incubator at 37°C under 5% CO_2_. Non-adherent cells will be removed when the medium is exchanged on days 5 to 7. When primary MSCs reach 70% to 80% confluence, they will be harvested and subcultured. Autologous MSCs will be culture expanded to 1 × 10^6^ cells/kg, the human dose equivalent to doses found to be effective in a rat stroke model (1 × 10^5^ to 3 × 10^6^ cells/rat) based on mean body weight [6]. Immediately before MSC infusion, 100 mL of 20% mannitol will be injected intravenously to open the BBB [43]. Expanded autologous MSCs at 1 × 10^6^ cells/kg (maximum 1.2 × 10^8^) will be transplanted through the antecubital vein with 5 × 10^6^ cells/mL of normal saline over 10 minutes. We will use good manufacturing practice conditions (Pharmicell Corporation, Seongnam, South Korea) and clinical grade reagents for cell preparation.

Cell viability will be determined by trypan blue staining at the end of harvest and before infusion, whether the viability is greater than 95%. Cell cultures will be tested weekly for bacterial, fungal, viral, or mycoplasmal contamination. Since stem cells are highly likely to be differentiated, the surface expression of CD105, CD90, CD73 (positive MSC markers), and CD34 (a negative MSC marker) will be measured on culture-expanded MSCs using flow cytometry (FACScan; Becton-Dickinson, Rutherford, NJ, USA) before intravenous transplantation into each patient. Each MSC harvest is expected to yield a homogenous population of cells with high expression of positive markers (>90% of cells) and low expression of the negative marker (<1% of cells).

#### Randomization and outcomes

Randomization will be in a 2:1 ratio of MSC-treatment to control patients using computer-generated random-permuted blocks with blocks of six subjects. The 2:1 ratio was selected to obtain a sufficient number of participants for explorative analysis in the MSC group. For the primary outcome analysis, the categorical shift in mRS at 90 days after treatment will be determined as 0 to 5 mRS levels. Deaths (a mRS score of 6) will be included in the category of worst outcome (a mRS score of 5). Secondary and exploratory outcomes are shown in Table 3.

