## Methods and design

### The STARTING-2 trial

#### Trial characteristics and design

STARTING-2 is the first study to evaluate the efficacy of MSC treatment in patients with ischemic stroke. The study is a prospective, randomized, open-label, blinded-endpoint (PROBE) clinical trial. Both acute and chronic cases of stroke will be included, and followed for 3 months after MSC treatment. The ratio of MSC-treated to control patients is 2:1. Patients will intravenously receive autologous MSCs after *ex vivo* culture expansion with autologous ischemic serum obtained as early as possible to enhance the therapeutic efficacy (ischemic preconditioning). Selection of patients will be based on clinical and radiological features, excluding patients with large involvement of periventricular regions. BBB manipulation using intravenous mannitol before MSC treatment and comprehensive and objective measurements using multimodal MRI and detailed functional assessments will be performed.

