#### Patient population and evaluation

The clinical trial protocol and consent form were approved by the Korean FDA and the Institutional Review Board of the Samsung Medical Center. Written informed consent will be obtained from all patients and/or their first-degree relatives. Inclusion and exclusion criteria are shown in Table 2. During the inpatient rehabilitation period, all participants will receive conventional rehabilitation therapy (physical, occupational, speech/language, or cognitive rehabilitation therapy as needed). Investigators blinded to treatment allocation will measure neurological disability using the NIHSS and functional scores for mRS and mBI. Motor parameters will be evaluated by the Motricity index and Fugl-Meyer assessment for gross motor function, Purdue pegboard test and box and block test for fine motor function, and functional ambulatory category and 10-m gait speed tests for mobility, for further demonstration and characterization of motor recovery [56-60]. Cognition (Mini-Mental Status Examination (MMSE)) and quality of life (EuroQol Five Dimensions (EQ-5D) questionnaire) tests will also be administered. Any complications or adverse effects observed during the study period will be described in detail. Flow diagrams of the study protocol are shown in Figures 2 and 3.

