## Trial status

Start date: November 2012.

Expected end date: February 2016.

Expected publication date: May 2016.

Status at time of submission of this article: recruitment ongoing.

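### A single published block size of six in an open-label trial still recruiting makes up to 29% of allocations deducible in advance, an avoidable exposure to selection bias

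*Protocol article*

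**What the plan says.** Under *Randomization and outcomes* the protocol article states: "Randomization will be in a 2:1 ratio of MSC-treatment to control patients", and that this is done "using computer-generated random-permuted blocks with blocks of six subjects". One block size is given. The section mentions neither variation of the size nor stratification.

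Four other statements bear on how visible the sequence is:

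- *Trial characteristics and design*: "The study is a prospective, randomized, open-label, blinded-endpoint (PROBE) clinical trial". Outcome assessment is blinded; treatment is not.
- *Preparation and transplantation of MSCs*: "Aspiration will be performed within 1 week after randomization to the MSC group". Control patients have no aspiration, so each allocation shows itself soon after it is made.
- *Trial status*: "Status at time of submission of this article: recruitment ongoing". The block size was therefore made public before the last patient was randomized.
- *Patient population and evaluation*: the protocol was "approved by the Korean FDA and the Institutional Review Board of the Samsung Medical Center". No other institution's board is named.

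The planned size is in *Sample size and statistical analysis*: "Approximately 60 participants (MSCs vs control group = 40:20) will be studied". On entry, Table 2 (inclusion 5a) asks for "Reasonable likelihood of receiving standard physical, occupational and speech rehabilitation therapy". Other items ask whether the patient can comply, and leave some comorbidity exclusions to the investigator's opinion.

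**The concern.** With a fixed block of four MSC and two control, the remaining allocations in a block are settled once four MSC or two control patients have been seen. Concealing the list does not help, because the next arm is worked out from past open allocations and a known block size. The sixth patient of every block is always determined.

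A recruiter who knows the next arm can hold, hurry or decline a candidate. Table 2 gives some room for this: several criteria need judgement, stroke onset may be up to 90 days back, and NIHSS may range from 6 to 21, so eligible patients differ widely in prognosis.

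The plan's safeguards act elsewhere. Blinded endpoint reading protects assessment, not entry. Intention-to-treat analysis preserves whatever comparison enrolment has produced. The primary model adjusts for age, sex, stroke mechanism and infarct volume, but not for baseline NIHSS or mRS, so it would remove steering on visible severity only in part. With 20 controls, a few steered patients count.

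**Working it through.** **Inputs from the article.** Block size 6; ratio 2:1, hence 4 MSC + 2 control per block; 60 patients, 40:20.

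**The plan's own figure.** 60/6 = 10 complete blocks; 10 × 4 = 40 MSC and 10 × 2 = 20 control. The stated 40:20 reproduces exactly.

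**Allocations known with certainty.** There are 15 orderings of a 4 + 2 block. An allocation is determined once the other arm's places are used up, so the determined allocations form the run of identical arms that ends the block.

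| Block ends in | Run of 1 | Run of 2 | Run of 3 | Run of 4 | Determined allocations, summed |
|---|---|---|---|---|---|
| MSC | 4 orderings | 3 | 2 | 1 | 4 + 6 + 6 + 4 = 20 |
| Control | 4 orderings | 1 | – | – | 4 + 2 = 6 |

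- Per block: (20 + 6)/15 = 26/15 = 1.733. The closed form agrees: 4/(2+1) + 2/(4+1) = 1.333 + 0.400.
- Share: 1.733/6 = 28.9%.
- Over 10 blocks: 17.3 of 60, made up of 13.3 MSC and 4.0 control.
- The last two or more are known in 7/15 = 46.7% of blocks, and the last three or more in 3/15 = 20%.

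**Best guess at every step.** Guess the arm with more places left, and count a tie as one half. Over the 15 orderings this is right for 67/15 = 4.467 of 6, or 74.4%. Always guessing MSC is right for 4 of 6, or 66.7%. The gain is (0.744 − 0.667) × 60, or about 4.7 patients.

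**Illustrative effect on the primary result.** The article gives no steering size and no mRS distribution, so both are assumed. Suppose patients in the determined slots are shifted by +0.5 log-odds of prognosis when the slot is MSC and by −0.5 when it is control, with no steering elsewhere and no true effect.

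- MSC mean shift: (13.33/40) × 0.5 = 0.167.
- Control mean shift: (4/20) × (−0.5) = −0.100.
- Difference: 0.267; exp(0.267) = 1.31 as the null odds ratio.

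Simulated unadjusted analyses of 60 patients on six mRS levels gave a type I error of 8.1% to 9.1%, depending on the test and the assumed mRS distribution. With no steering, an unadjusted proportional-odds simulation gave 5.4% to 5.8% (1,500 trials, standard error about 0.6 points). The excess is about 3 percentage points.

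**After a change of block scheme.** Simulated for staff who see every allocation, know the set of sizes and update after each patient:

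| Scheme | Known with certainty | Best guess right |
|---|---|---|
| Fixed 6 | 28.9% | 74.4% |
| Fixed 9 | 21.4% | 72.8% |
| Fixed 12 | 17.0% | 71.7% |
| Random 3/6/9 | about 4% | about 74% |
| Random 6/9/12 | about 2% | about 72% |

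**The case against.** The strongest reply is that the figure is conditional. It needs one unstratified sequence, known block starts, and recruiters who track every earlier allocation. The article states none of these outright; a single sequence is inferred from one named review board and from silence on stratification in a condensed article. Several sites sharing one list without seeing each other's allocations would know less. This stands, and 28.9% is an upper-end figure.

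The information gained is also smaller than the headline suggests. Some 13 of the 17 determined slots are MSC, which the ratio already makes 67% likely. This stands too.

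Four stronger readings are tempting, and the document does not support them.

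- *That the trial is biased.* Nothing in the article shows that anyone steered enrolment.
- *That slow recovery is another judgemental criterion.* Table 2 (4d) defines it as a numerical NIHSS change over three days. Severity, motor scores and lesion size are numerical as well. Discretion is confined to items such as likelihood of rehabilitation, ability to comply and some comorbidity.
- *That type I error is inflated by a known amount.* ±0.5 is a contrast of 1.0 log-odds between patients steered to the two arms, applied to every determined slot, which is not small. At ±0.25, simulated error (about 6%) cannot be told apart from the unsteered baseline. The prespecified adjusted model would absorb some of the shift.
- *That list concealment is missing.* An article commonly leaves to the full protocol who holds and releases the list. The point here rests only on the block size that is stated.

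**Conclusion.** The point holds as a design weakness in a rule the article fixes, not as an error or a contradiction. One known block size, visible allocations and publication during recruitment make the sequence partly deducible, however well the list itself is hidden. Under full tracking of a single sequence, up to 28.9% of allocations are certain in advance and best-guess success is 74.4% against 66.7%.

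The count of 26/15 per block is exact. The consequences for the odds ratio (about 1.3) and the type I error (about 8% against 5% to 6%) are illustrations that depend on assumed steering and an unadjusted analysis. The exposure is worth removing because that is cheap; it does not by itself invalidate the trial.

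**What to change.** For all remaining allocations, replace the fixed block with randomly varying sizes in multiples of three, for example 6, 9 and 12, or 3, 6 and 9. Do not disclose the sizes to recruiting staff, and do not publish them until recruitment ends. A larger block that is still fixed and known is a weaker remedy (17.0% certain at size 12).

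The gain should be stated without exaggeration. Certain knowledge falls to about 2% to 4% even if the set of sizes leaks, but best-guess success falls only to about 72% to 74%. The change removes certainty rather than guessing, and works best while the sizes stay unknown. Of the two examples, 6/9/12 does better on both measures.

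The cost is a regenerated list for the remaining patients, and a final split that may miss exactly 40:20 by a patient or two, which a target of approximately 60 can accommodate. Treatment, eligibility, endpoint and analysis are unchanged.
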